## Abstract

**Background:**

Massive resources are expended every year on cross-cultural communication training for physicians. Such training is a focus of continuing medical education nationwide and is part of the curriculum of virtually every medical school in America. There is a pressing need for evidence regarding the effects on patients of cross-cultural communication training for physicians. There is a need to understand the added benefit of such training compared to more general communication. We know of no rigorous study that has assessed whether cross-cultural communication training for physicians results in better health outcomes for their patients. The current study aims to answer this question by enhancing the Physician Asthma Care Education (PACE) program to cross cultural communication (PACE Plus), and comparing the effect of the enhanced program to PACE on the health outcomes of African American and Latino/Hispanic children with asthma.

**Methods/Design:**

A three-arm randomized control trial is used to compare PACE Plus, PACE, and usual care. Both PACE and PACE Plus are delivered in two, two-hour sessions over a period of two weeks to 5–10 primary care physicians who treat African American and Latino/Hispanic children with asthma. One hundred twelve physicians and 1060 of their pediatric patients were recruited who self-identify as African American or Latino/Hispanic and experience persistent asthma. Physicians were randomized into receiving either the PACE Plus or PACE intervention or into the control group. The comparative effectiveness of PACE and PACE Plus on clinician’s therapeutic and communication practices with the family/patient, children’s urgent care use for asthma, asthma control, and quality of life, and parent/caretaker satisfaction with physician performance will be assessed. Data are collected via telephone survey and medical record review at baseline, 9 months following the intervention, and 21 months following the intervention.

**Discussion:**

This study aims to reduce disparities in asthma outcomes among African American and Latino/Hispanic children through cross-cultural communication training of their physicians and assessing the added value of this training compared to general communication. The results of this study will provide important information about the value of cross-cultural training in helping to address persistent racial disparities in outcomes.

**Trial registration:**

ClinicalTrials.gov: NCT01251523 December 1, 2010

## Background

Asthma affects 7.1 million U.S. children and is the main reason children use urgent care services for a chronic disease [1]. In 2009, 1 in 5 children with asthma sought care in an emergency department [2]. Asthma prevalence among children and adolescents is estimated to be 9.6% overall, and is highest among non-Hispanic black children (17.0%) [2]. Hispanic/Latino and non-Hispanic black children have greater asthma-related risk exposures than non-Hispanic Whites, and are at higher risk for emergency department visits, hospitalizations, and death from asthma [3-6]. They exhibit lower adherence to medication and only about one-third report using long-term controller medicine or receiving asthma care plans from their clinicians [2]. Poor outcomes are especially striking among African American children, who have a 260% higher emergency department (ED) visit rate, a 250% higher hospitalization rate, and a 500% higher death rate from asthma than their White counterparts [7]. Because the risk, severity, and control of asthma are all influenced by a combination of genetic, social, and environmental factors, reducing the impact of the condition has proven difficult. However, enhancing clinical care in populations with marked disparities is regarded as a priority effort [8,9]. Asthma is most often managed in the primary care setting and 80% of those affected never visit an asthma specialist [2]. Given the high prevalence of asthma in children and the associated frequency of visits to primary care practitioners, these health care providers are the asthma patients’ primary source of care and education. Thus improving asthma clinical care in primary care providers offers the potential to reduce the burden of asthma in underserved populations.

The uncertainty of physicians in their interactions with minority patients, the clinicians’ beliefs or stereotypes regarding the health behavior of minority patients, and patient response to perceived negative experiences with providers all have been discussed extensively in the literature [10]. The dramatic demographic shifts occurring in the United States mean that increasing numbers of minority patients are being seen in the health care system and, for the foreseeable future, the majority of the physicians who treat them are unlikely to be of their same racial or ethnic background. Further, it is increasingly expected that health care institutions account for the social and cultural diversity of the U.S. population [11] especially as it relates to clinical practice, and performance expectations for practicing physicians are also very high.

Massive resources are expended every year on cross-cultural communication training for physicians. Such training is a focus of continuing medical education nationwide and is part of the curriculum of virtually every medical school in America. There is a pressing need for evidence regarding the effects on patients of cross-cultural communication training for physicians. There is a need to understand the added benefit of such training compared to training in more general communication and patient-physician partnership skills [12]. However, we know of no rigorous study that has assessed whether cross-cultural communication training for physicians results in better health outcomes for their patients.

### Adapting the Physician Asthma Care Education Program

The Physician Asthma Care Education (PACE) Program is a two-part interactive, multi-media educational seminar developed two-decades ago and widely disseminated to improve physician awareness, ability, and use of communication and therapeutic techniques for reducing the effects of asthma on children and their families. Efficacy and effectiveness trials have shown that patients of PACE-trained physicians demonstrate improvements in long-term outcomes including fewer symptoms and less health care use [13,14]. Importantly, no more time is required in the patient-physician encounter by PACE-trained physicians. This general communication intervention provides an effective comparison to investigate the added value of training in cross-cultural communication. PACE was enhanced to focus on cross-cultural communication training. This enhanced intervention, PACE Plus, was developed with cultural anthropology experts and piloted on three occasions with 31 primary care physicians. Unpublished data reveal that the majority of participants believed the training to be very useful and relevant, and participants demonstrated significant improvement in their understanding of cross-cultural communication, and increased confidence in engaging in tailored communication with underserved populations.

## Methods/Design

This study used a randomized controlled design with three arms: control, the original PACE intervention, and PACE Plus intervention (enhanced with cross-cultural communication training) to test the comparative effectiveness of PACE with cross-cultural communication training, a proven asthma-based communication intervention for physicians. All study procedures were reviewed and approved by the University of Michigan Health Sciences and Behavioral Sciences Institutional Review Board (IRB-HSBS HUM#00030087).

### Study hypotheses

The study addressed two questions: 1) Does cross-cultural communication training (PACE Plus) produce better outcomes for African American and Latino/Hispanic children with asthma, and their respective parents, than a general communication training program (PACE)?; 2) Compared to the control group, is PACE, already shown to be effective with the general population of patients, effective when used specifically with African American and Latino/Hispanic children with asthma, and their parents?

The study hypothesis is that there will be positive outcomes for patients of physicians in both interventions but better outcomes for those patients whose doctors participate in the cross-cultural communication training (PACE Plus). That is, PACE Plus compared to PACE will result in reductions in children’s health care use for asthma, improved symptom experience for the children, greater parent/caretaker satisfaction with the physician’s performance, enhanced asthma related quality of life for parents/caretakers of the patients, higher levels of confidence and value placed by physicians on skills needed when working cross culturally, and increased use of National Asthma Education and Prevention Program (NAEPP) recommended therapies by physicians. It is also hypothesized that PACE compared to a control group will produce better outcomes on the aforementioned, six dimensions.

### Sample size determination

The sample size of 1002 children and their parents total at baseline was determined by power calculations using the primary outcome of proportion of subjects with emergency department (ED) visits in the last twelve months taking into account a 25% attrition rate over 24 months leaving 801 total subjects at the end of the study. The sample size calculation is based on the assumption that the clustering of patients within physician practices is negligible, which is justified from the previous PACE study [14]. In that prior research, the intracluster correlation values were close to zero (0.24 at the physician level; 0.003 at the site level). In analysis, such correlation will be adjusted for, if necessary. In the previous PACE study [14], the baseline proportion of patient participants with an ED visit was 30% and this was decreased by 15% in 24 months. For the current study, there will be 80% power to detect a more conservative difference of 12% or more in the proportion of patient participants with an ED visit in 24 months at the significance level of 0.05.

In the previous PACE study, those in the intervention group decreased by a little more than one mean emergency office visit and 0.09 mean hospitalizations [14]. With the sample size in the current study, there will be statistical power to detect changes at that level for hospitalization and at much lower levels than in the previous PACE study for emergency office visits. Given the relatively rare occurrence of emergency department visits, the sample size needed to detect changes is relatively large; this gives an advantage in having sufficient statistical power to detect small changes in other outcomes, including symptoms, patient satisfaction and asthma related quality of life.

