#### *Child and parent recruitment*

A total of 1,060 patients were recruited from the pool of patients provided by enrolled physicians. To be eligible, the child needed to meet the inclusion criteria listed in Table 1 and their parent or caregiver needed to meet the eligibility criteria as well.

Initially, the office staff of a participating physician was asked to provide a list of patients who met the eligibility criteria using office records. The patient list was provided to research staff. Eligible patients/caretakers were then mailed a recruitment packet containing a cover letter from the participating physician inviting them to enroll, a study overview page, two copies of the consent form, a health information screener form, a decline postcard, and a stamped self-addressed envelope for returning a copy of the consent and screener form.

Following the mailed information, patients received recruitment phone calls, which provided information about the study’s purpose, design, randomization, and data collection. Calls were made by trained bilingual staff, to ensure the same information was provided to all potential participants. Participants could opt to complete the consent and screener via paper and mail them back, via telephone with a trained staff member. Once consent was received by the research staff, parents were contacted by a telephone interviewer and scheduled for a baseline interview. The recruitment scripts, consent forms, and the telephone interviews were available in both English and Spanish. Children/parents subsequently followed physicians into one of the three study arms as randomized. Parents were not informed if their physician was participating in the intervention.

The following ongoing strategies were employed to enhance recruitment and retention. 1) caretakers received a $30 gift card following completion of the baseline data-collection interview and a $20 gift card for each subsequent completed follow-up interview; 2) Mother’s and Father’s Day cards were mailed annually to maintain a personal connection; 3) a study newsletter, mailed bi-annually, provided updates on study progress and basic asthma information; 4) repeated attempts were made over a year to check for reconnected phone lines; 5) the study team maintained contact with physician offices and periodically asked for updated contact information for enrolled participants.

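### The baseline of 1002, the 25% attrition and the 801 completers do not agree: 25% attrition from 1002 leaves about 752

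*Protocol article*

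**What the plan says.** The protocol article, under Sample size determination, gives the three figures in one sentence.

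- Baseline: "The sample size of 1002 children and their parents total at baseline".
- Loss and number remaining: "taking into account a 25% attrition rate over 24 months leaving 801 total subjects at the end of the study".

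The same paragraph gives the power claim for the proportion of children with an ED visit: "there will be 80% power to detect a more conservative difference of 12% or more", "in 24 months at the significance level of 0.05". The only ED rate it supplies is 30% at baseline, taken from the previous PACE study.

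Enrolment is reported elsewhere as complete. Child and parent recruitment says "A total of 1,060 patients were recruited from the pool of patients provided by enrolled physicians", while the Randomization section gives 1062 patients.

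**The concern.** The baseline and end-of-study figures are both totals over the same children, and a single attrition rate is meant to link them. It does not. No other section gives a different rate, a different base or an intermediate step that would reconcile them. All three figures are printed, so this is not detail left to an unseen analysis plan.

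Two things are at stake. A reader cannot tell whether 20% or 25% loss was planned. And the end-of-study number given beside the 80% power claim is about 50 children larger than the stated baseline and attrition deliver.

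**Working it through.** **Inputs from the article**

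- Sample size determination: baseline N = 1002; attrition d = 0.25; stated completers 801; power 80%; significance level 0.05; ED baseline 30%; difference to detect 12%.
- Methods/Design: three arms.
- Child and parent recruitment, and Randomization: 1,060 and 1062 enrolled.

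**Assumptions**, because the article does not state them: equal arms; a two-sided test; the 12% read as percentage points. Clustering is ignored, as the article's own calculation does.

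**1. Can 801 be reproduced?** Completers = N × (1 − d).

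- 1002 × 0.75 = 751.5, about 752 in total and about 250 per arm. The stated 801 is not reproduced.
- Gap: 801 − 751.5 = 49.5 children, or 49.5 / 801 = 6.2%. Rounding cannot account for this.
- Implied attrition: 1 − 801/1002 = 0.2006, or 20%.

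**2. What calculation gives the printed pair?**

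- Multiplying: 801 × 1.25 = 1001.25, rounded up to 1002. Per arm, 267 × 1.25 = 333.75, rounded up to 334, and 3 × 334 = 1002.
- Dividing, which is the correct inflation: 801 / 0.75 = 1068 (356 per arm), which is 66 more than 1002.

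The multiplication matches exactly, both in total and per arm.

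**3. Effect on power.** For two proportions with n per arm, difference D and mean proportion p̄:

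power = Φ{ [D√n − 1.96 √(2p̄(1−p̄))] / √(p₁(1−p₁) + p₂(1−p₂)) }

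For 30% versus 18%: p̄ = 0.24, √(2 × 0.24 × 0.76) = 0.604, √(0.21 + 0.1476) = 0.598.

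- n = 267: (0.12 × 16.340 − 1.184) / 0.598 = 1.299, power 90.3%.
- n = 250: (0.12 × 15.811 − 1.184) / 0.598 = 1.193, power 88.4%.

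Under the same assumptions, 80% power needs 198 per arm (594 in total), so 250 per arm is well clear of it.

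**4. Sensitivity to an assumed higher event rate.** These rates are not in the article.

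- 50% versus 38%: 79.9% at 267 per arm, 77.3% at 250.
- 56% versus 44%: 79.4% at 267 per arm, 76.7% at 250.

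**5. Reported enrolment at 25% attrition**

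- 1060 × 0.75 = 795, which is 6 below 801.
- 1062 × 0.75 = 796.5, about 797, which is 4.5 below 801.
- Keeping 801 of 1,060 would mean 1 − 801/1060 = 24.4% attrition.
- With 795 / 3 = 265 per arm and 30% versus 18%: (0.12 × 16.279 − 1.184) / 0.598 = 1.287, power about 90%.

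**The case against.** The strongest reply accepts the arithmetic and disputes its importance. At the only ED rate the article gives, the error costs about two points of power and the 80% claim still holds. Enrolment passed 1002 and, at 25% loss, comes within about 6 children of 801. Recruitment is reported in the past tense, so no design decision still depends on the planned figure. All of this stands, and it is why the point is minor. It does not make the printed sentence correct.

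A reader might be tempted to go further in three ways.

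- **That the error leaves the trial below its stated power.** Power falls under 80% only with event rates near 50%, and the article contains no such case. Its word conservative describes 12% against the 15% decrease in the previous study, not a 50% event rate. That 50% versus 38% comes close to 267 per arm may hint at where 801 came from, but it is no evidence that the plan used it.
- **That multiplying by 1.25 is the established cause.** The match is exact and the inference is strong, but the article does not show the step. An intended 20% attrition that was misprinted would also nearly fit, since 1002 × 0.80 = 801.6.
- **That every power statement rests on 801.** The second paragraph of the section refers only to the sample size of the current study, without saying whether the baseline or the final number is meant, and gives no numerical power for the other outcomes.

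**Conclusion.** The inconsistency is certain: with 1002 at baseline, 25% attrition leaves about 752, not 801, and 801 corresponds to 20% attrition. The gap is about 50 children (6%), or about 17 per arm.

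The consequence is small. For 30% versus 18%, power is about 88% instead of 90%, and reported enrolment brings the expected completers back to about 795 to 797. These power figures assume a two-sided 0.05 test, equal arms, a 12-point absolute difference and no clustering. Whether clustering can be ignored is a separate question, and this point neither depends on it nor settles it.

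This is a minor correction of a stated sample-size figure. It does not show that the trial is too small.

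**What to change.** In Sample size determination, keep 1002 and either state about 752 completers at 25% attrition, or state 20% attrition with 801 completers if that was the intended rate. Then restate power on the completers expected from actual enrolment: about 795 from 1,060, or about 797 from 1062, at 25% attrition. Give the assumed proportions and the sidedness of the test alongside it.

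Replacing 1002 with 1068 is not a workable correction. It would print, after recruitment closed, a target that the article never stated and that enrolment did not reach.

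The cost is one corrected sentence and one rerun of the power figure, with no new recruitment and no change to the design.

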### Analysis

Analyses will involve both discrete (dichotomous, counts, ordinal) and continuous (measurable) variables. Analysis techniques utilized will be based on the type of variables, categorical or continuous. Initially, descriptive statistics for the characteristics of the sample for each group will be produced. Then t tests/Wilcoxon rank test, chi-squared tests and Fisher’s exact test will be used to detect potential differences on demographic and practice variables between three randomized groups. If differences are found, adjustments in post-test measures, via subgroup and covariance analyses, will be made. Adjusted comparisons, controlling for variables that relate to the outcome will be performed using multivariate regression techniques. Adjusting for variables that relate to the outcome will increase the efficiency of the estimates by reducing the residual error, and correct for bias due to association between drop outs and these variables.

Separate analyses of physicians’ characteristics related to each of the communication and cultural competence skills will be conducted. Multiple logistic regression will be used for dichotomous variables in each analysis with group assignment as an independent variable. Changes in the physicians’ use of specific NAEPP recommended therapies will be examined through logistic regression.

Analyses of the parent interview data will be conducted to assess outcomes that are related to four categories of variables: 1) changes in the child’s health care use for asthma 2) changes in the child’s symptom status 3) changes in parents’ views of physician performance; and 4) increase in asthma-related quality of life for parents. For changes in parents’ views of physician counseling, multiple logistic regression will be used for each analysis with group assignment as an independent variable. The role of patient age and gender, severity of illness, tobacco exposure (as this is associated with increased asthma symptoms), patient insurance (private, Medicaid, or self-pay status), and other relevant influences will be identified for appropriate inclusion in models.

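### Adjustment for correlation within physician is left conditional, with no criterion, although physicians are the randomised unit

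*Protocol article*

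**What the plan says.** The Randomization section assigns 112 physicians to the arms: 44 to PACE, 36 to PACE Plus and 32 to control. Under Child and parent recruitment, "Children/parents subsequently followed physicians into one of the three study arms as randomized".

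The Sample size determination section rests on "the assumption that the clustering of patients within physician practices is negligible". It supports this from the previous PACE study, where "the intracluster correlation values were close to zero (0.24 at the physician level; 0.003 at the site level". It then states the rule for the analysis: "In analysis, such correlation will be adjusted for, if necessary". Nothing says what would make adjustment necessary, who decides, or when.

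The Analysis section names tests for comparing demographic and practice variables between the groups, regression in general terms for adjusted comparisons, and logistic regression for physician variables. For parents' views of physician counselling, "multiple logistic regression will be used for each analysis with group assignment as an independent variable". It names no specific model for health care use, the primary outcome, and no method for clustered data for any outcome.

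**The concern.** When physicians are randomised, children of the same physician share both the arm and whatever that physician and practice contribute to the outcome. The variance of an arm comparison therefore contains a between-physician component by design, and whether to include it should not turn on the data. A rule with no criterion leaves that choice open until results are in hand.

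The text also hints at how the choice might be made. An ICC of 0.24 is treated as negligible for the sample size. If the same standard were applied at analysis, adjustment could be judged unnecessary at a value where it changes the inference substantially.

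At stake is the validity of every patient-level comparison, including the main question of whether PACE Plus improves on PACE. Parents' ratings are an obvious case, since several parents rate the same doctor.

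**Working it through.** **Inputs (protocol article)**

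- Significance level: "at the significance level of 0.05"; the number of sides is not stated, and two-sided is assumed.
- ICC at physician level: 0.24 (Sample size determination).
- Physicians: 112 (Physician and parent recruitment).
- Children: 801 expected at the end of the study (Sample size determination); 1060 recruited (Child and parent recruitment).
- Assumed: equal numbers of children per physician. Unequal numbers would increase the inflation.

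**The plan's own figures.** The 5% level is correct for an unadjusted test only if the design effect is 1, which is what the sample size assumption amounts to. The planned numbers do not follow from the stated inputs: 30% against 18% at two-sided 5% and 80% power needs 198 per arm (594 in total), and 801 / 3 = 267 per arm gives 90.3% power. That is a separate matter. The check below uses 801 only to obtain the number of children per physician.

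**Children per physician (m)**

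- 801 / 112 = 7.15
- 1060 / 112 = 9.46

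**Design effect (DE) = 1 + (m − 1) × ICC**

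- m = 7.15: 1 + 6.15 × 0.24 = 2.48
- m = 9.46: 1 + 8.46 × 0.24 = 3.03

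**Standard error too small by a factor of √DE:** √2.48 = 1.57 and √3.03 = 1.74. Unadjusted 95% intervals are too narrow by the same factors.

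**True type I error of the unadjusted test = 2 × (1 − Φ(1.96 / √DE))**

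| ICC | m | DE | 1.96/√DE | Type I error |
|---|---|---|---|---|
| 0.24 (as printed) | 7.15 | 2.48 | 1.25 | 21.3% |
| 0.24 (as printed) | 9.46 | 3.03 | 1.13 | 26.0% |
| 0.024 (if 0.24 is a misprint; assumed) | 7.15 | 1.15 | 1.83 | 6.7% |
| 0.024 (if 0.24 is a misprint; assumed) | 9.46 | 1.20 | 1.79 | 7.4% |
| 0.003 (the site-level value, for scale) | 7.15 to 9.46 | 1.02 to 1.03 | 1.94 | 5.2% to 5.3% |

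The stated 25% attrition from 1002 would leave 1002 × 0.75 = 751.5, not 801. With that number m = 6.71 and the error at ICC 0.24 is 20.3%, so the conclusion does not depend on which figure is right.

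**Simulation.** Beta-binomial outcomes with p = 0.30, 44 against 36 physicians and an unadjusted two-proportion test (20,000 runs) gave 21.5% with 7 children per physician and 25.2% with 9 at ICC 0.24, and 6.9% and 7.5% at ICC 0.024. This agrees with the formula.

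**If the rule meant testing for clustering first.** A further simulation (10,000 runs per setting, all 112 physicians) applied a one-way F test within arm at 5%, then a physician-level t test of PACE against PACE Plus if clustering was detected and the unadjusted test if not. Ranges are for 7 to 9 children per physician.

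| ICC | Clustering detected | Type I error of the two-step procedure |
|---|---|---|
| 0.024 | 30% to 42% | about 5.8% |
| 0.05 | 70% to 86% | about 5.6% |
| 0.10 | 99% to 100% | about 5% |
| 0.24 | 100% | about 5% |

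**The case against.** The strongest reply is that the article does promise adjustment where it is needed. With 112 physicians, any formal check would find an ICC of 0.24 practically every time, and testing first and adjusting when clustering is found keeps the error below about 6%. On that reading, 21% to 26% is a worst case in which the investigators see strong clustering and still ignore it. This stands as a limit on the figure, which applies only if adjustment is skipped. It does not rescue the rule, because the article commits to no check and no threshold, and describes 0.24 as near zero.

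Second, 0.24 sits badly with that description and may be a misprint. This also stands. The documents cannot settle it, so both values are shown; some inflation remains at 0.024.

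Third, a reader might infer that the primary outcome is committed to an ordinary logistic regression without a physician term. The Analysis section does not support that. It ties logistic regression to physician variables, where clustering of patients does not arise, and to parents' views, and it ties the simple tests to demographic and practice variables. An article may leave the choice of mixed model or GEE to a fuller plan, so silence on the method is not the fault. The stated condition is.

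A reader might also infer that a false claim for PACE Plus is likely. It is not: even in the worst case the 21% to 26% is two-sided, so about 11% to 13% would favour PACE Plus on any one outcome.

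**Conclusion.** The point holds as a fault in a stated rule. In a trial that randomises physicians, accounting for physician should not be conditional, and here the condition has no criterion and stands beside a description of 0.24 as negligible. Followed as written, the plan permits patient-level tests that are not valid.

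If adjustment is skipped, type I error is about 21% to 26% instead of 5%, and intervals are too narrow by a factor of 1.57 to 1.74. This assumes that 0.24 is correct and applies to the outcome tested, that clusters are equal in size and that tests are two-sided. If the true value is 0.024, the error is about 7%.

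**What to change.** In Sample size determination, replace the conditional sentence with a firm one, for example: *All patient-level outcomes will be analysed with a method that accounts for clustering by physician (a mixed model with a physician random intercept, or GEE with robust variance and a small-sample correction), whatever the observed intracluster correlation.*

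In the Analysis section, say the same for every patient-level outcome, including health care use and parents' views. Analyses with one record per physician need no change on this account.

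Check 0.24 against the previous PACE study and either correct it or stop describing it as close to zero.

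The change is to wording and needs no new patients or data. Its cost is wider confidence intervals, which the design already implies. At ICC 0.24 the cost in power is real: with 801 children the effective number is 267 / 2.48 = about 108 per arm, and power for 30% against 18% is about 54%. Leaving the adjustment out would not recover that power validly.
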